# Systematic medical assessment, referral and treatment for diabetes care in China using lay family health promoters: protocol for the SMARTDiabetes cluster randomised controlled trial

**DOI:** 10.1186/s13012-016-0481-8

**Published:** 2016-08-17

**Keywords:** Type 2 diabetes, Capacity strengthening, mHealth, China, Implementation

## Abstract

**Background:**

Type 2 diabetes (T2DM) affects 113.9 million people in China, the largest number of any country in the world (JAMA 310:948–59, 2013). T2DM prevalence has risen dramatically from around 1 % in the 1980s to now over 10 % and is expected to continue rising. Despite the growing disease burden, few people with T2DM are achieving adequate management targets to prevent complications. Health system infrastructure in China is struggling to meet these gaps in care, and innovative, cost-effective and affordable solutions are needed. One promising strategy that may be particularly relevant to the Chinese context is improving support for lay family members to care for their relatives with T2DM.

**Methods:**

We hypothesise that an interactive mobile health management system can support lay family health promoters (FHP) and healthcare staff to improve clinical outcomes for family members with T2DM through medical assessment, regular monitoring, lifestyle advice and the prescribing of guidelines recommended medications. This intervention will be implemented as a cluster randomised controlled trial involving 80 communities (40 communities in Beijing and 40 rural villages in Hebei province) and 2000 people with T2DM. Outcome analyses will be conducted blinded to intervention allocation.

The primary outcome is the proportion of patients achieving ≥2 “ABC” goals (HbA1c <7.0 %, blood pressure (BP) <140/80 mmHg and LDL cholesterol <100 mg/dl or 2.6 mmol/L) at the end of follow-up (Diabetes Care 36(Supplement 1):S11-S66, 2013). Secondary outcomes include the proportion of patients achieving individual ABC targets; mean changes in HbA1c, BP, LDL, renal function (serum creatinine and urinary albumin), body mass index, quality of life (QOL, EQ-5D), and healthcare utilisation from baseline; and cost-effectiveness/utility of intervention. Trial outcomes will be accompanied by detailed process and economic evaluations.

****Discussion**:**

The Chinese government has prioritised prevention and treatment of diabetes as 1 of 11 National Basic Public Health Services. Despite great promise for mHealth interventions to improve access to effective health care, there remains uncertainty about how this can be successfully achieved. The findings are likely to inform policy on a scalable strategy to overcome sub-optimal access to effective health care in China.

**Trial registration:**

Clinicaltrials.gov NCT02726100

## Background

### Diabetes disease burden and healthcare quality gaps

China has experienced a dramatic increase in the prevalence of type 2 diabetes (T2DM) from around 1 % in the 1980s to now over 10 %. It is home to the largest number of diabetics in the world [1, 2]. The health system has struggled to keep pace with this rapid rise in disease burden. Despite well-established evidence on effective strategies to reduce death and disability from diabetes, its uptake into routine medical care remains limited [3, 4]. In China, it has been estimated that fewer than 10 % of diabetes patients are achieving target HbA1c, blood pressure and low-density lipoprotein (LDL)-C levels [5]. A study from Chaoyang, the biggest district in Beijing, estimated that only about 2 % of patients with hypertension or diabetes received standard care or management [6]. Exclusive reliance on a highly trained medical workforce to address this is not sustainable. Innovative, scalable implementation strategies are therefore urgently needed.

### Evidence of self-management and interactive technology interventions for T2DM

One promising solution is to increase self-management support and build the capacity of lay family members to provide improved diabetes care. Systematic reviews of self-management strategies have demonstrated improvements in diabetes outcomes with reductions in HbA1c of about 0.5 % [7–9]. There is also growing evidence of the contribution of information technology (IT)-based interventions (internet, mobile, decision support and telemedicine) to improving diabetes self-management. A recent systematic review of 104 studies (60 randomised trials) demonstrated improvements in outcomes in 73 % of studies [10]. Despite these promising outcomes, most self-management and lay-support interventions have generally been restricted to high-income countries. Given the highly varied health system and socio-cultural contexts in China, there are major opportunities to generate evidence of effectiveness from self-management and family-based diabetes interventions that are supported by IT strategies.

### Working with family health promoters

Support for people with chronic diseases in China is traditionally provided by children and grandchildren. Although family members are highly motivated to care for relatives, much of this care is variable in quality and not evidence-informed. In 2008, the family health promoter (FHP) project was commenced, in which a voluntary family member received training in chronic disease management and took responsibility for maintaining the health of the whole family. Community health service practitioners were engaged to deliver professional support to these FHPs [11, 12]. Significant improvements in behaviour change, blood pressure and blood glucose control were achieved. In a study involving 11,192 family members, the FHP intervention was associated with a 29.3 % improvement in knowledge scores at 6 months which was sustained at 12-month follow-up [11, 12]. Two randomised controlled trials (102 patients in Beijing and 220 patients in Zhejiang) showed that FHP-based disease management significantly lowered fasting plasma glucose by 0.7 mmol/l compared to usual care (*p* < 0.01) [13, 14]. Publicly praised by the Beijing government, the FHP initiative was recognised as a “Beijing Government Serving People Project” and has planned to train at least 20,000 FHPs each year since 2011 [15]. Despite the success of the trials, the scale-up phase of the programme is experiencing difficulty in sustainability, primarily due to excessive demands on medical staff to support its uptake. Key problems include: (1) a requirement of staff to attend a 12-class training workshop; (2) competing demands with routine clinical work and (3) provision of training and ongoing support to FHPs once enrolled in the programme.

### Previous research using mobile health

Mobile health (mHealth) technologies offer an unprecedented opportunity to address these three questions. In 2012, there were 380 million smartphone users in China, now surpassing the USA to become the leading country for active Android and iOS subscribers [16]. In a recently completed pilot study in two rural China provinces, we found that around 90 % of patients’ close family members have access to mobile phones, and over 50 % of these are smartphones. The SimCard study tested whether training village doctors in the use of an Android application could help support the management for people with cardiovascular disease (CVD) [17]. The intervention was tested in Tibet and rural India in a recently completed 47 village cluster randomised controlled trial (RCT) and demonstrated a 24 % improvement in prescribing of recommended medications. In India, a trial is currently underway of a multifaceted system involving training community health workers to perform village-based CVD risk screening using an Android tablet and uploading data for review and management by the treating primary healthcare doctor. The intervention is being tested in a stepped-wedge cluster RCT involving 18 primary healthcare centres, 54 villages and over 15,000 people at high CVD risk [18]. In Australia, the TORPEDO trial of a provider-focussed decision support system and quality improvement intervention found a 10 % absolute improvement in CVD risk factor measurement and a 17 % improvement in guideline recommended prescribing of medicines to people at high CVD risk who were not taking these medicines at baseline [19].

In this study, we harness these previous initiatives to offer an innovative strategy for addressing the diabetes epidemic in China—SMARTDiabetes.

### Research methods

SMARTDiabetes will be conducted in two phases, and specific aims are as follows:Phase 1: intervention developmentTo conduct a comprehensive barriers analysis of the existing Family Health Promoter project to understand the opportunities and constraints experienced by patients with T2DM and their families in accessing high quality health careTo develop an evidence-based appraisal of best practice recommendations for the management of T2DM and develop these into a health management algorithmTo take a user-centred design approach with urban and rural patients, family health promoters and medical staff to develop and field-test the health management ‘app’
Phase 2: implementation and evaluationTo conduct a large-scale cluster randomised controlled trial of the system and determine its clinical impact for people with T2DMTo conduct process and economic evaluations to understand intervention impact on patients, FHPs and staff and to determine cost-effectiveness and scale-up opportunities

## Methods/design

### Methods—phase 1

#### Barrier analysis

A comprehensive barriers analysis of the existing Beijing FHP project will be conducted and expanded to one rural province (Hebei) to understand contextual constraints on provision of best practice care. Normalisation Process Theory [20] and the Behaviour Change Wheel [21] will be used to understand the extent to which the intervention was incorporated into routine practice and to assess the capabilities, opportunities and motivation of medical staff, families and patients to obtain improved outcomes related to diabetes. Data sources will include document analysis, process mapping work with stakeholder groups and semi-structured individual interviews.

#### Incorporation of clinical guidelines

Best practice recommendations will be provided based on Chinese national and international guidelines to support self-monitoring of blood pressure and blood glucose, lifestyle change (smoking cessation, weight loss, improved diet, aerobic exercise, alcohol and sodium restriction), adherence to medical treatments and prevention of complications. These will then be programmed into a prototype application for use via desktop computer and mobile device and validated using methods that we have used previously [22].

#### User-centred prototype development

We will then engage platform users (FHPs, patients, doctors and nurses) in the design and development of the prototype applications. User scenarios will be clarified, and the routine workflow patterns that will best engage medical staff and FHPs will also be determined. An agile software development approach will be taken in which prototypes are developed, tested and rapidly re-deployed based on user feedback. Over several cycles, the prototype will progress from low-fidelity (paper-based) concepts to an eventual high-fidelity clickable prototype that will resemble the final product. Once the prototype is finalised, software development of the complete solution will be conducted.

#### EHR integration

In Beijing, a large provider of community health service electronic platforms will be involved in the development of SMARTDiabetes. In Hebei province, we propose a hybrid approach utilising a stand-alone cloud-based system where electronic health record (EHR) uptake is low and an integrated system where EHRs are readily used.

#### Feasibility study and implementation optimisation

Two communities will be selected from Beijing and Hebei to pilot test its feasibility, validity and stability of the platform. Although the exact usage scenarios will not be clarified until the above scoping work is completed, a typical work flow pattern might include the following features (Fig. 1):

**Fig. 1 Fig1:**
[figure not shown]
Key elements of the intervention package

A training and support package will be developed to guide healthcare workers and FHPs on use of the technology and management of diabetes.An initial medical consultation with a nurse or doctor will be scheduled, and personalised health information will be entered into either a stand-alone application or directly into the local EMR used at the health service. An assessment of micro- and macrovascular risk, hypoglycaemic risk and management principles will then be generated. The assessment will then be uploaded to a cloud-based electronic medical record.The FHP will download the consumer version of the SMARTDiabetes application and register as a user. The application will be available on a mobile device or as a web page on a desktop computer. The FHP will then create an account for the family member whom they would like to look after.The consumer version of the SMARTDiabetes app will pre-populate with information from the cloud-based EMR. An action plan wizard will assist FHPs in making personalised health goals and targets for their relatives. Automatic prompts and warnings will be triggered by SMARTDiabetes based on clinical needs, the co-determined action plan and the patients’ progress. Adjustments of action plan could be made any time by the FHPs on behalf of the patient, and data in the EHR will be refreshed with the latest information.A forum feature will also be built where multiple users within the community will be able to share experiences with one another.The patient’s nominated care provider will also be given an authorised view of the application to assist with health care for use at subsequent health centre visits. All routine medical care will otherwise continue as usual.

Following field testing, the intervention will be optimised in preparation for trial implementation.

### Methods—phase 2

#### Hypothesis

An interactive mobile health management system can support lay family health promoters and healthcare staff to improve clinical outcomes for family members with T2DM, and this system will be affordable, acceptable and potentially scalable across China.

#### Design

This study is a community-based parallel-arm cluster RCT (Fig. 2).

**Fig. 2 Fig2:**
[figure not shown]
Study schema

#### Setting

The trial will involve 2000 participants from 80 communities in one urban (Beijing province) and one rural setting (Hebei province). Geographically dispersed communities will be selected within provinces to minimise contamination risk. Each community health station must serve at least 1000 adult residents, and clinical staff at the station must be willing to participate in the trial.

#### Participants eligibility

Eligible participants will then be recruited from these sites. They must have established T2DM, be aged 40 years and above and be meeting no more than one of the following American Diabetes Association “ABC” management targets (HbA1C < 7 %; blood pressure < 140/80 mmHg, LDL cholesterol < 100 mg/dl or 2.6 mmol/L). Participants must also be able to provide informed consent and have a nominated family member who is willing to serve as FHP and has access to a smartphone or internet-enabled desktop computer. The FHP need not be living with the family member. Given many parents, particularly in rural villages, have children working in cities, this criterion will enhance recruitment feasibility and external validity.

#### Randomisation

Communities will be centrally randomised in a 1:1 allocation, stratified by community size and location (urban/rural) to either receive the intervention or continue with usual health care.

#### Intervention

Participants in intervention communities will receive the SMARTDiabetes intervention as defined in Fig. 2 plus usual health care for 24 months. Medical staff and FHPs in the intervention communities will be provided with an initial training session on the installation and use of the platform. These staff will also register as healthcare providers in the system and will be able to track patient progress and provide support to FHPs via communication tools built into the application.

#### Control arm

Patients in the control arm communities will receive usual care provided by community health service system or hospitals. The only exception is that they will also be invited to take part in the survey and examination at baseline, mid-term (12 months) and end of study (24 months) for the purpose of evaluation. To avoid contamination of intervention, the SMARTDiabetes application will only be accessible for FHPs and medical staff in intervention communities via a secure password-protected registration process.

#### Data collection

We will invite participants in both the intervention and control groups to visit the nearby Community Health Service Center to receive a comprehensive survey, standard anthropometric measures and blood collection at baseline, mid-term (12 months) and end of study (24 months). In both Beijing and Hebei, a qualified central laboratory will be selected to conduct standard laboratory tests for all the participants. Table 1 below outlines the data that will be collected. Although it will be difficult to ensure complete blinding of data collectors to community allocation status, these staff will not be involved in the implementation of the intervention. Primary outcome data will be obtained from objective reports (e.g. printable blood pressure readings and pathology laboratory readings), and a proportion of the total sample will be audited for accuracy.

**Table 1 Tab1:** Data collection procedures

Assessment description	Screening	Baseline/randomisation	12-month visit	Final visit
Informed consent	X			
Eligibility	X	X		
Reasons for non-participation	X	X		
Demographics, medical history,		X		
Medications, physical examination, vital signs, vital status^a^		X	X	X
Quality of life questionnaire		X	X	X
Laboratory results^a^		X	X	X
Serious adverse events		X	X	

^a^End point evaluation data derived from these data elements

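### Table 1 as printed schedules serious adverse events at baseline and 12 months but not at the 24-month final visit, leaving non-fatal events in the second year without a scheduled collection point

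*Protocol article*

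**What the plan says.** The Data collection section introduces the schedule with the statement "Table 1 below outlines the data that will be collected". The table has four visit columns: screening, "Baseline/randomisation", a 12-month visit and a final visit. The row "Serious adverse events" has a mark under baseline/randomisation and one under the 12-month visit. Its cells for screening and the final visit are empty.

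The row beginning "Medications, physical examination, vital signs, vital status" is marked at baseline, 12 months and the final visit. So are the rows for the quality of life questionnaire and for laboratory results.

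The Intervention section gives intervention communities the programme "plus usual health care for 24 months". The Data collection and Control arm sections bring participants of both arms in at baseline, 12 months and 24 months, so the final visit is month 24. SAEs are mentioned nowhere else in the article, and it has no safety section.

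**The concern.** The two marks sit where they are least useful. An event recorded at baseline precedes any exposure and says nothing about the intervention. The visit that closes the second year, and at which the primary outcome is measured, has no SAE item. SAE is the only follow-up row that stops halfway.

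The question is not idle for this intervention. It aims to move patients towards HbA1c, blood pressure and LDL targets through monitoring, prompts and prescribing, and the assessment generated at the first consultation includes hypoglycaemic risk. If forms are built from this table, staff will have no prompt at month 24 to ask about serious events since month 12. Such events are hard to recover reliably once that visit has passed. An account of harms by arm would then cover the first year only, while benefit is judged at two years.

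**Working it through.** The document states no figure on this point, so there is none to reproduce. The check is a reading of the table against the trial's timeline, followed by simple arithmetic on the size of the gap.

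**1. Is the row read correctly?** The table came through text extraction, so a shifted column had to be considered. Each of the 8 rows was split on its column separators. Each gives 5 cells, matching the 5 headers. The marks fall as follows.

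| Row | Screening | Baseline | 12 months | Final |
|---|---|---|---|---|
| Consent | X | | | |
| Eligibility | X | X | | |
| Reasons for non-participation | X | X | | |
| Demographics, history | | X | | |
| Medications, examination, vital signs, vital status | | X | X | X |
| Quality of life | | X | X | X |
| Laboratory results | | X | X | X |
| Serious adverse events | | X | X | |

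The SAE row has the right number of cells and the other rows align sensibly, so an extraction shift is unlikely. The typeset table should still be checked.

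**2. What period does the row cover?** The visits are at months 0, 12 and 24. A question at month 12 can cover months 0 to 12. Nothing is scheduled that covers months 12 to 24. The uncovered share of the intervention period is 12/24 = 50%.

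**3. Person-time.** The inputs are 2000 participants, 2 years of follow-up and 20% loss (Setting; Intervention; Statistical considerations).
- With no loss: 2000 × 2 = 4000 person-years, of which 2000 fall after month 12 (50%).
- With all of the 20% lost at the outset: 1600 × 2 = 3200, of which 1600 fall after month 12 (50%).
- With all of the 20% lost at month 12: 2000 + 1600 = 3600, of which 1600 fall after month 12 (44%).

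The gap is therefore 44% to 50% of planned person-time, depending on when losses occur, which the document does not say.

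**4. Precision of an SAE rate difference.** Suppose events are independent and occur at a constant rate. The variance of the rate difference is then λ₁/T₁ + λ₀/T₀, where λ is the event rate and T the person-time in each arm. Halving T doubles the variance, so the standard error rises by √2 = 1.41. This is an upper bound for a constant rate. With all losses at month 12 the ratio is √(3600/2000) = 1.34. Variation between the 80 communities, or between persons, adds a component that longer follow-up does not shrink, and this lowers the ratio further. No SAE rate is given, so the ratio cannot be tied to a planned analysis.

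**5. Does anything else at month 24 fill the gap?** Vital status records deaths. Healthcare utilisation is a secondary outcome and could reflect some admissions, but it is not an SAE item and has no row of its own in Table 1. The survey, examination, medication review and laboratory tests may reveal some serious events incidentally. None of these is a scheduled SAE question put identically in both arms.

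**The case against.** The strongest reply is that this is a journal article condensing a protocol that is not shown. The table only outlines the data, and the mechanics of SAE reporting are commonly left to the full document. Reporting may be event-driven and run throughout. The marks may also be a slip: a pair meant for 12 months and final set one column too far left, or a shorthand for collection that starts at randomisation. No sentence argues for ending SAE collection at month 12, so it should not be read as a deliberate choice.

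Much of this stands, and it limits what may be inferred. A reader might conclude that SAEs in the second year will go unrecorded. The article does not show that. A reader might also conclude that only deaths would be visible in that year. That is too strong, given the final-visit survey, examination and laboratory tests and the utilisation outcome. Nor does the gap defeat a stated objective, because no SAE comparison is listed among the primary or secondary outcomes.

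The reply does not remove the point. Leaving SAE procedures to the full protocol would be unremarkable, but here the article prints a schedule, and that schedule does not fit its own 24-month follow-up. If reporting is in fact continuous, or the marks are misplaced, the table misdescribes the plan and still needs correcting.

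**Conclusion.** The concern holds as a statement about Table 1 as printed. The SAE row conflicts with the 24-month intervention and with every other follow-up row, and no other part of the article supplies the missing collection. Followed literally, it leaves non-fatal SAEs in months 12 to 24 without scheduled, like-for-like capture in the two arms. The size is half of the intervention period, and 44% to 50% of planned person-time under the stated 20% loss. The loss of precision is at most 1.41-fold in the standard error, and only for independent events at a constant rate. The larger cost would be harms that appear only with longer exposure, which no gain in first-year precision can reveal.

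This rests on two assumptions: that the extracted table matches the typeset one, and that no unseen document schedules SAE collection in the second year. The primary outcome, sample size, power and type I error are not affected.

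**What to change.** Mark serious adverse events in Table 1 at both the 12-month and the final visit. State that each covers the period since the previous visit and is asked in the same way in both arms. Remove the baseline mark or relabel it as history. Report SAEs by arm over the full 24 months.

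If the full protocol already collects SAEs continuously, correct the table to say so and name the period covered.

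The cost is one table cell, one relabelled cell and one item on the final-visit form, at a visit that participants of both arms are already invited to attend. It should be settled before the final-visit forms are fixed.
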